### Data management and access

Data management and access will be restricted to study personnel approved by the Institutional Review Board. All data will be stored on secure, password-protected servers and encrypted in accordance with institutional data protection policies. Only the Principal Investigator and IRB-approved study team members will have access to the final trial datasets, including identifiable information, which will be stored separately from study data, linked through the participant study ID, and used solely for recruitment, scheduling, and follow-up communications. All individuals with access will be trained in confidentiality protocols and responsible data handling procedures. De-identified datasets will be used for analysis.

A formal Data Monitoring Committee is not planned due to the minimal-risk nature of this single-site, behavioral intervention [37]. Trial conduct and participant safety will be monitored by the Principal Investigator and Project Manager, who will independently and jointly review recruitment, retention, adherence, and any safety concerns on an ongoing basis.

### Sample size justification

Consistent with methodological guidance that pilot trial sample size should be large enough to estimate key feasibility parameters with acceptable precision, minimum sample size was determined based on feasibility objectives and progression criteria rather than testing for intervention efficacy [38].

A priori progression criteria were defined for recruitment, retention, session attendance in the MSC-LC condition, and treatment fidelity. Recruitment will be considered feasible if at least 50% of eligible participants enroll and not feasible if recruitment uptake is 33% or less. Retention will be considered feasible if 75% or more of participants complete follow-up assessments and not feasible if retention is 50% or less. MSC-LC attendance will be considered feasible if at least 60% of participants attend six or more sessions and not feasible if 33% or fewer attend six or more sessions. Treatment fidelity will be considered feasible if at least 80% of intervention components are delivered per session and not feasible if delivery is 50% or less. Using the normal approximation method for a two-arm parallel design with one-sided *α* =.05 and 90% power to evaluate these feasibility thresholds [38], the *minimum* required sample size was *n* = 62 (*n* = 31 per condition).

MSC-LC will be delivered across three planned cohorts, each designed to include approximately 10–15 participants to facilitate meaningful discussion and interpersonal exchange [14, 39]. Accordingly, total recruitment may range from 62 to 90 participants to ensure adequate group size across cohorts. Although the sample size is consistent with accepted conventions for pilot trials, we acknowledge that it limits the precision and generalizability of the quantitative findings. The analyses are intended to inform the design and feasibility of a future fully powered trial.

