#### Intervention feasibility and treatment fidelity (primary outcomes)

Feasibility will be assessed using three indicators, with the number of MSC-LC sessions each participant attends reflecting feasibility of the intervention itself and the number of eligible patients who enroll in the study (recruitment) and the number of questionnaire assessments completed by both MSC-LC and CTL participants (retention) reflecting feasibility of the research protocol for potential scale-up to a larger trial [43]. A priori benchmark indicators to assess feasibility (and treatment fidelity) are listed below in the Data Analysis plan.

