### Data analysis

#### Quantitative analyses

Range checks will be conducted to identify missing, aberrant, or out-of-range values, which will be reviewed and resolved by the study team. Descriptive statistics (means, standard deviations, frequencies) will be reported for all study variables, and zero-order correlations will be examined to assess associations among outcomes and mediators. Key clinical characteristics (e.g., disease stage, smoking history) will be described across study arms and explored in relation to primary outcomes (e.g., session attendance) to inform future trial design. Analyses will be conducted using Stata v19.

The primary outcomes of interest are feasibility and acceptability indices; clinical and psychosocial outcomes will be considered secondary exploratory outcomes. Progression criteria were established a priori to classify outcomes as feasible, in need of amendment, or not feasible based on predefined thresholds. Feasibility will be evaluated using descriptive statistics. The intervention will be considered feasible to deliver if at least 60% of participants in the MSC-LC condition attend six or more sessions, reflecting meaningful engagement while accounting for common attendance barriers in oncology populations; it will be considered not feasible if 33% or fewer meet this threshold. Recruitment will be considered feasible if at least 50% of eligible participants (with lung cancer diagnosis confirmed via medical record) agree to enroll and be randomized, and not feasible if recruitment uptake is 33% or less. Retention will be considered feasible if at least 70% of participants remain in the study through the post-intervention assessment and not feasible if 50% or fewer are retained. Treatment fidelity adherence will be considered adequate if ≥80% of predefined intervention components are delivered per session, ensuring that the intervention is delivered with sufficient integrity, and not considered feasible if fidelity adherence is 50% or less. Fidelity via interventionist competence will be deemed sufficient if the mean MSC TAC rating across the three sampled sessions per cohort and per interventionist is greater than or equal to 4 (“competent”) with no individual domain less than 3 (“advanced beginner”). We will also report the proportion of ratings at or above 5 (“proficient”) as an indicator of intervention quality.

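### The sample size of 62 does not come from a two-arm calculation as described: it matches a doubled one-sample test of a single criterion, and its 90% power cannot apply to all four feasibility thresholds

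*Protocol article*

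**What the plan says.** The Sample size justification sets a feasible and a not-feasible value for each of four criteria:

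- Recruitment: "Recruitment will be considered feasible if at least 50% of eligible participants enroll and not feasible if recruitment uptake is 33% or less".
- Retention: "Retention will be considered feasible if 75% or more of participants complete follow-up assessments and not feasible if retention is 50% or less".
- Attendance of six or more sessions in the MSC-LC condition: 60% against 33%.
- Fidelity: "Treatment fidelity will be considered feasible if at least 80% of intervention components are delivered per session", with 50% or less counted as not feasible.

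It then gives the method, "Using the normal approximation method for a two-arm parallel design with one-sided" alpha of .05, and the claim "90% power to evaluate these feasibility thresholds", and arrives at a minimum of 62, or 31 per condition. Total recruitment may range from 62 to 90. The section does not say which criterion sets the figure or why it is expressed per condition.

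Other sections fix the denominators. The section on primary outcomes counts retention over both arms: "the number of questionnaire assessments completed by both MSC-LC and CTL participants (retention"). It defines adherence as the share of predefined session components delivered, rated from recordings. The intervention has 10 sessions and is planned in three cohorts.

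The retention target differs elsewhere. Quantitative analyses has "Retention will be considered feasible if at least 70% of participants remain in the study through the post-intervention assessment", and the Aims section allows attrition of 30% or lower.

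**The concern.** The four criteria are the primary outcomes and decide whether the programme progresses, so the basis of the sample size ought to be checkable. Read literally, a two-arm calculation compares a proportion between MSC-LC and CTL. None of the criteria does that: each sets one proportion against fixed values. Attendance exists in one arm only, recruitment is counted on eligible people, and fidelity is counted on sessions and their components. One participant number cannot carry the same 90% power for all of them. A reader will nevertheless take 90% as holding for each, and cannot tell from the text which criterion led to 31.

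**Working it through.** **Inputs.** One-sided alpha .05 (z = 1.645) and 90% power (z = 1.282), with the threshold pairs from the Sample size justification (p0 = not feasible, p1 = feasible). The 70% retention target is from Quantitative analyses.

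**Step 1: reproduce the plan's figure.** One-sample normal approximation:

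n = [1.645·√(p0(1−p0)) + 1.282·√(p1(1−p1))]² / (p1−p0)²

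For retention, 50% against 75%: [1.645 × 0.500 + 1.282 × 0.433]² / 0.25² = (0.822 + 0.555)² / 0.0625 = 30.35, so 31. Doubled, this is 62, exactly the stated minimum.

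**Step 2: the same formula for every criterion, beside the two-sample size per arm.**

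| Criterion | p0 v p1 | One-sample n | Two-sample n per arm (unpooled / pooled) |
|---|---|---|---|
| Retention, 75% target | 50 v 75 | 30.35 → 31 | 60 / 63 |
| Retention, 70% target | 50 v 70 | 49.68 → 50 | 99 / 101 |
| Attendance | 33 v 60 | 26.93 → 27 | 55 / 57 |
| Recruitment | 33 v 50 | 69.20 → 70 | 140 / 142 |
| Fidelity, units taken as independent | 50 v 80 | 19.80 → 20 | 40 / 42 |

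No two-sample entry is 31. Continuity correction only raises those sizes (retention at 75% becomes 71 per arm).

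**Step 3: is retention the only source of 31?** No. With the one-sample continuity correction, n′ = (n/4)·[1 + √(1 + 2/(n(p1−p0)))]², attendance gives 26.93 → 30.53, so 31. The text mentions no correction, so uncorrected retention is the simpler match, but attendance cannot be excluded.

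**Step 4: power on each criterion's own denominator with 62 enrolled.** Normal approximation: power = Φ{[(p1−p0)√n − 1.645√(p0(1−p0))] / √(p1(1−p1))}. Exact values use the smallest binomial cutoff with one-sided alpha at or below .05.

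| Criterion | Denominator | Normal approximation | Exact |
|---|---|---|---|
| Attendance, 33 v 60 | 31 in MSC-LC | 93.2% | 87.2% (≥16 of 31) |
| Retention, 50 v 75 | 62 randomized | 99.6% | 99.4% (≥38 of 62) |
| Retention, 50 v 70 | 62 randomized | 95.0% | 94.6% (≥38 of 62) |
| Recruitment, 33 v 50 | 62 / 0.50 = 124 eligible | 98.7% | 98.1% (≥51 of 124) |

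For attendance, the exact cutoff at 31 uses only 2.5% of the alpha. At n = 30 the exact test has 90.3% power (≥15 of 30, alpha 4.0%). The drop from 30 to 31 reflects the discreteness of the binomial.

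**Step 5: fidelity.** 10 sessions × 3 cohorts = 30 sessions. Randomizing more people into the same cohorts adds no session and no rated component, so this criterion has no power that depends on 62.

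**The case against.** The strongest reply is that 62 does reproduce: 31 from a one-sample calculation, times two. On that view the two-arm phrase merely describes the trial for which a per-condition number is doubled, and the method is cited to a source not at hand. This largely stands. Doubling also has a basis, because attendance is measured in one arm of a 1:1 trial, so about 30 in MSC-LC means about 60 randomized. For retention, counted over both arms, doubling is simply generous.

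A second reply is that feasibility will be judged descriptively, that 62 is a minimum, and that the article already concedes limited precision. That limits the consequences. It does not make the stated method or the blanket 90% correct, and both are statements in the article rather than detail left to another document.

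Two stronger readings are tempting and should not be drawn. One is that the trial needs 120 to 126 participants (2 × 60 to 2 × 63). That size tests a difference in retention between arms, which the plan never poses; it shows only that the two-arm wording cannot be taken literally. The other is that attendance is underpowered because its exact power is 87%. By the method the article names it is 93%, and the exact shortfall is mostly discreteness at n = 31.

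**Conclusion.** The description of the calculation is wrong as written, while the number enrolled is not shown to be inadequate. The minimum of 62 equals twice a one-sample size for a single criterion, most simply retention at 75% against 50%. The 90% power cannot be a common property of four criteria with different denominators, and for fidelity it has no meaning in terms of participants. If retention did set the figure, it was set with a target that the Aims and Quantitative analyses do not use; at 70% the one-sample size is 50, still within the 62 to be randomized.

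On the denominators above, 62 enrolled gives at least 90% power by the normal approximation for attendance, retention at either target, and recruitment. This assumes independent participants, all 62 counted for retention, 31 in the MSC-LC arm, and 50% uptake for the 124 eligible people. Which criterion produced 31 is an inference from the arithmetic; the article does not say.

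**What to change.** Revise the Sample size justification, with no change in enrolment:

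1. Describe the calculation as one-sample tests of each proportion against its not-feasible value, and drop the two-arm description of the method.
2. Name the criterion that sets 31, say whether a continuity correction was used, and state that the figure is doubled because of 1:1 allocation.
3. Give power by criterion on its own denominator and label the method: attendance on 31 in MSC-LC, 93% by normal approximation and 87% exact; retention on all 62 randomized, over 99% at a 75% target or 95% at 70%; recruitment on about 124 eligible people at 50% uptake, about 98%.
4. Use one retention target throughout the Sample size justification, Aims and Quantitative analyses, with the same definition of being retained.
5. Remove fidelity from the participant-based power statement and describe it by sessions and components.

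The cost is a rewritten paragraph and one aligned threshold.

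### The stated 90% power is power to rule out the not-feasible rates; it is not the chance that a programme at target is classified feasible, which is about 50%

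*Protocol article*

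**What the plan says.** The section Sample size justification sets two bounds for each progression criterion. Attendance is feasible if "at least 60% of participants attend six or more sessions and not feasible if 33% or fewer attend six or more sessions". On retention it states: "Retention will be considered feasible if 75% or more of participants complete follow-up assessments and not feasible if retention is 50% or less". Recruitment has bounds of 50% and 33%, and fidelity 80% and 50%. The calculation then follows for all four together: "Using the normal approximation method for a two-arm parallel design", with a one-sided alpha of .05 "and 90% power to evaluate these feasibility thresholds", the minimum "required sample size was *n* = 62 (*n* = 31 per condition". Null, alternative and critical value are not named.

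The section Quantitative analyses gives the decision rule. "Feasibility will be evaluated using descriptive statistics". The intervention counts as feasible to deliver if "at least 60% of participants in the MSC-LC condition attend six or more sessions"; results at or below the lower bound are not feasible, and those between need amendment. Recruitment and retention are handled the same way, but the retention threshold there is 70%. The rule contains no test, critical count or confidence bound.

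**The concern.** Alpha and power describe a test. The printed rule compares a point estimate with a cutoff. The two can behave very differently at the same true rate, because a test against the lower bound rejects well short of the upper threshold.

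Feasibility is the primary outcome, and it informs whether and how a larger trial is designed. A reader who sees 90% power tied to the feasibility thresholds may take it that a programme performing exactly at target has a 90% chance of the *feasible* label. If the real chance is near one half, an *amendment* result would be misread as evidence that the programme fell short.

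**Working it through.** **Inputs.** From Sample size justification: one-sided alpha .05, power 90%, 31 per arm and 62 in total (recruitment may reach 90), attendance 33%/60%, retention 50%/75%, recruitment 33%/50%. From Quantitative analyses: retention threshold 70%. Denominators: attendance uses the MSC-LC arm (31), retention both arms (62), recruitment the eligible people. The last is not given; 124 is assumed, since 62 / 0.50 = 124.

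**Step 1: reproduce 31 per arm.** Take the lower bound p0 as null and the upper bound p1 as alternative, one sample, one-sided:

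n = [(1.645·√(p0(1−p0)) + 1.282·√(p1(1−p1))) / (p1−p0)]²

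- Attendance: [(1.645 × 0.470 + 1.282 × 0.490) / 0.27]² = 26.9. With continuity correction, (n/4)(1 + √(1 + 2/(n(p1−p0))))² = 30.5, so 31.
- Retention 50% vs 75%: [(1.645 × 0.500 + 1.282 × 0.433) / 0.25]² = 30.4, so 31 without correction (34.2 with it).

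Doubling 31 for 1:1 allocation gives 62. Other readings miss. A one-sided comparison of two proportions needs 57 per arm for attendance and 63 for retention (64 and 71 corrected). A two-sided one-sample test needs 33 and 38 (37 and 42 corrected). So the 90% is most plausibly power to reject the *not feasible* rate. This is inferred from the reproduction, and which criterion drove the number cannot be settled, because attendance (corrected) and retention (uncorrected) both give 31.

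**Step 2: where that test rejects (attendance, n = 31).** The normal cutoff is 0.33 + 1.645·√(0.33 × 0.67/31) = 0.469. Power at 60% is 0.93 uncorrected and 0.90 corrected. The exact binomial critical count is 16/31 (51.6%), with exact alpha 0.025 and exact power 0.87.

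**Step 3: the printed rule.** Attendance of at least 60% of 31 means 18.6, so 19/31 (61.3%). Exact binomial probabilities when the true rate equals the threshold:

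| Criterion | n | Count needed | P(*feasible*) | P(*not feasible*) |
|---|---|---|---|---|
| Attendance 60% | 31 | 19 | 0.52 | 0.002 |
| Attendance 60% | 45 | 27 | 0.56 | <0.001 |
| Retention 75% | 62 | 47 | 0.51 | <0.001 |
| Retention 70% | 62 | 44 | 0.50 | <0.001 |
| Retention 75% | 90 | 68 | 0.51 | <0.001 |
| Retention 70% | 90 | 63 | 0.55 | <0.001 |
| Recruitment 50% | 124 (assumed) | 62 | 0.54 | <0.001 |

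Recruiting to the maximum of 90 does not change the picture.

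**Step 4: true rates giving a 90% chance of *feasible*.** Attendance about 70% (n = 31). Retention about 81% for the 75% threshold or 77% for the 70% threshold (n = 62). Recruitment about 55% (124 eligible, assumed).

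**Step 5: power to rule out *not feasible* for the other criteria.** Retention, n = 62, reject at 38 or more: exact power 0.994 at a true 75%, 0.946 at 70%. Recruitment, 124 eligible, reject at 51 or more: 0.98.

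**Fidelity.** Its unit is session components delivered, so 31 participants per arm is not its sample size and no comparable probability follows from the document.

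**The case against.** The strongest reply is that nothing printed is false. The number 62 reproduces, so this is not an arithmetic error. The 87% exact figure differs from 90% only because the protocol names the normal approximation. The article speaks of evaluating thresholds and never promises a 90% chance of the *feasible* label. A probability near one half at a cutoff holds for any point-estimate rule at any sample size. The three zones separate their bounds well: for attendance at n = 31, P(*feasible*) at a true 33% is 0.001 and P(*not feasible*) at a true 60% is 0.002. The article also acknowledges limited precision.

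Most of this stands, and it limits the point. What remains is that the article justifies its sample size by alpha and power tied to these thresholds, does not say which decision that power describes, and then prints a rule to which it does not apply. Both statements are in the text, so this is not something left to an analysis plan.

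Four stronger readings are tempting but unsupported:

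- That an on-target programme would probably be rejected. Missing the upper threshold normally means *amendment*.
- That meeting all criteria together is very unlikely. Each criterion is classified separately; no rule requires all to pass, and multiplying the probabilities would also assume independence.
- That fidelity too is a coin toss. Its unit does not allow that calculation.
- That clustering by cohort invalidates the power. The document gives no intraclass correlation, so any loss depends wholly on an assumed value.

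**Conclusion.** The concern holds in a limited form. The 90% is defensible as approximate power to rule out the *not feasible* rate when the true rate equals the *feasible* rate. It is not the probability of the *feasible* classification, which is 0.50 to 0.56 for attendance, retention and recruitment at the planned sizes when the true rate is exactly at the threshold.

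This rests on an inferred null hypothesis, independent participants, and 124 eligible people for recruitment. The attendance and retention probabilities for the printed rule do not depend on the inferred null. Severity is moderate: the sample size and the three zones can stay, but the only sample size justification and the primary decision rule should describe the same thing.

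**What to change.** 1. In Sample size justification, state that the design gives about 90% power (normal approximation; 87% exact for attendance at n = 31) to rule out the not-feasible rate when the true rate equals the feasible rate. Name the criterion or criteria that give 31 per arm, and take fidelity out of that statement.
2. In Quantitative analyses, keep the three zones but report each rate with an exact confidence interval. Add that *not feasible* is ruled out when the one-sided 95% lower bound exceeds the not-feasible rate. Compute the critical count for the number actually achieved, since recruitment may run from 62 to 90: for example attendance 16/31 or 21/45, and retention 38/62 or 54/90.
3. State that the point-estimate *feasible* zone has about a 50% probability when the true rate lies on the threshold.
4. Use one retention threshold in both sections (now 75% and 70%).

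An attendance analysis allowing for cohort, under a stated assumed intraclass correlation, is an optional sensitivity analysis.

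The cost is wording and a few binomial calculations, with no extra participants. The downside is that the stated power will read less favourably.

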### Interventionists

Each cohort of the MSC-LC intervention will be delivered by two Certified MSC teachers who have completed the core MSC curriculum, a 12-week Teacher Training, and a 10-week Teacher Training Practicum, have co-taught the MSC curriculum with consultation from a senior MSC teacher, subsequently taught at least three additional MSC courses, and received at least 14 h of individual mentorship from a senior MSC teacher over the course of teaching an additional two MSC courses [40]. The interventionists will also receive a 90-min training on the MSC-LC adaptation, which includes an overview of lung cancer stigma definitions and examples, relevant research on tailoring MSC to this population, as well as guidance on modifying language and offering flexible options for breathwork and movement practices to better meet participants’ needs and lived experiences [14]. Interventionists will also participate in weekly supervision with the PI to review participant concerns and support trauma-sensitive and culturally responsive intervention delivery.

